# Effectiveness of a high-intensive trauma-focused, family-based therapy for youth exposed to family violence: study protocol for a randomized controlled trial

**DOI:** 10.1186/s13063-021-05981-4

**Published:** 2022-01-17

**Keywords:** Family violence, Domestic violence, Posttraumatic stress, Intensive, Children, Parent, Security, Safety, Trauma, Relationship

## Abstract

**Background:**

Family violence is a common problem with direct adverse effects on children as well as indirect effects through disruption of parenting and parent-child relationships. The complex interrelationships between family violence, parenting, and relationships make recovery from psychological responses difficult. In more than half of the families referred to mental health care after family violence, the violence continues. Also, the effect sizes of “golden standard” treatments are generally lower for complex trauma compared to other forms of trauma. In the treatment of complex trauma, trauma-focused therapies including cognitive restructuring and imaginal exposure are most effective, and intensifying therapy results in faster symptom reduction. Furthermore, there is promising evidence that adding a parental component to individual trauma treatment increases treatment success. In family-based intensive trauma treatment (FITT), these factors are addressed on an individual and family level in a short period of time to establish long-term effects on the reduction of trauma symptoms and recovery of security in the family. This randomized controlled multicentre study tests if FITT is an effective treatment for concurrent reduction of trauma symptoms of children, improvement of parenting functioning, and increasing emotional and physical security in children, through the improvement of parent-child relationships.

**Methods:**

The effectiveness of FITT will be tested by a RCT design. A total of 120 adolescents with a history of family violence and PTS symptoms will be randomized to (a) an intensive trauma treatment with a parent and systemic component (FITT), (b) an intensive trauma treatment without these components (ITT), and (c) treatment as usual (TAU, low-frequency trauma treatment with parent therapy and family sessions). Changes in children’s trauma symptoms, child and parent functioning, and emotional and physical security in the family will be monitored before, during, after, and at 3 months follow-up.

**Discussion:**

Comparing these interventions with and without a high intensive frequency and parenting and family components can help to understand if and how these interventions work and can contribute to the ambition to recover from the impact of family violence and restore emotional and physical security for children and young people.

**Trial registration:**

Netherlands Trial Register Trial NL8592. Registered on 4 May 2020

## Administrative information

Note: the numbers in curly brackets in this protocol refer to SPIRIT checklist item numbers. The order of the items has been modified to group similar items (see http://www.equator-network.org/reporting-guidelines/spirit-2013-statement-defining-standard-protocol-items-for-clinical-trials/).

## Introduction

### Background and rationale {6a}

#### The prevalence and impact of family violence

Family violence is a common problem and affects children and their families. In the Netherlands, almost 6% of the population aged 18 and older experienced some incident of family violence over the 5 years prior to the study [1]. In 2018, it was estimated that between 26 and 37 children and youth up to age 18 years per 1000 were victims of child maltreatment; in almost half of these cases, child maltreatment happened in a context of family violence, mostly between parents [2]. Family violence has a strong adverse impact on children, both immediately and in the long term, across somatic and psychological domains [3]. Children can experience problems in multiple domains of functioning [4] and are at risk to develop posttraumatic stress (PTS) symptoms [5]. Besides direct effects of exposure to family violence, the association of family violence with parenting and the parent-child relationship indirectly increases the risk of maladaptive developmental pathways (5–7). Family violence has an impact on parents’ mental health, such as PTS disorder [6] and depression [7]. Parental PTS can mediate the effect of violence on parenting behaviour [8], and higher levels of parental stress are associated with higher levels of children’s PTS [5]. The influence of family violence on children, parents, and thereby on parenting and the parent-child relationship makes family violence a complex problem. Effect sizes of “golden standard” trauma treatments are generally lower for childhood trauma like family violence than for other forms of trauma [9]. With regard to long-term safety in the family, in more than half of the families referred to mental health care after family violence, the violence was still severe or occurred frequently one and a half years later [10]. This indicates a need for interventions for the whole family system that address long-term safety.

#### Direct pathway: the effects of family violence on children

Family violence has a direct effect on children’s functioning. After exposure to family violence children can develop posttraumatic stress symptoms, anxiety, and depressive symptoms [11, 12]. Almost a quarter of young children exposed to family violence develop posttraumatic stress (PTS) symptoms at clinical levels and another 16% in the subclinical range [5]. In a referred sample, 21% of children exposed to family violence had clinical posttraumatic stress symptoms [13]. Children’s direct responses to violence have been conceptualized using cognitive context theory [14]. According to this theory, violence is perceived as a stressor, leading to cognitive appraisal and selection and generation of coping responses. Contextual, cognitive, and developmental factors determine children’s appraisal and ensuing responses to family violence. For example, children who consider the violence as a negative event and attribute the conflict to themselves can experience more stress than children who consider the conflict as unimportant or attribute the conflict to others or the circumstances [14]. According to emotional security theory (EST) [15], children try to maintain a sense of safety and security within the family system, which may lead to emotional, behavioural, and cognitive short-term adaptations that may be maladaptive in the long run and outside the context of the family. In reaction to the violence, children show intense distress (emotional reactivity) [16], avoidance of or involvement in the conflict (behavioural regulation) [17, 18], and update their internal representations of the integrity of the family and the risk that they are running to become a target of violence themselves (cognitive response) [19]. Children can become more vulnerable to psychological problems if they experience prolonged difficulties in achieving and maintaining safety and security within the family system [20].

#### Indirect pathway: the effect of family violence on parents and family relationships

In addition to direct effects, family violence may also indirectly cause emotional and behaviour problems in children through parenting and family relationships. According to the EST, family violence leads to parenting difficulties that negatively influence the parent-child relationship and the representation of the parent-child relationship and undermine children’s well-being. Exposure to family violence has been linked to more negative and less positive parenting compared to parenting in non-violent families [21]. Parents involved in family violence showed more harsh discipline towards their children [21], were less supportive, showed less effective parenting [22], were less emotionally available [23, 24], and used more psychological control towards their children [25, 26]. These parenting difficulties make it difficult for children to see their parents as a source of protection and support. For example, maladaptive parenting mediates the relationship between family violence and children’s internalizing problems [27]. Furthermore, there is evidence for the association of family violence with a disturbed parent-child interaction [23, 24]. High levels of parental unavailability in combination with high levels of family violence are associated with insecure representations of the parent-child relationship, and these representations are associated with children’s engagement difficulties at school [24]. Also, the magnitude of the association between family violence and children’s internalizing problems is dependent on the degree of parental warmth and availability [27].

#### Treatment after family violence

International guidelines for children (AACAP, 2010; NICE, 2018) recommend individual trauma-focused cognitive behavioural therapy (TF-CBT) and eye movement desensitization and reprocessing (EMDR) after traumatic events, like family violence. On average, TF-CBT and EMDR are effective in addressing PTS symptoms of children [28]. However, treatment effect sizes were generally lower for different forms of childhood maltreatment like family violence, compared to single-event trauma [9]. Furthermore, most studies on complex trauma focused on TF-CBT for adults instead of children, and in general, the number of trials with EMDR was limited. In contrast to EMDR, TF-CBT is a multicomponent treatment consisting of non-trauma-focused and trauma-focused components. When treating adults with complex trauma, trauma-focused therapies that include cognitive restructuring and imaginal exposure are most effective [29]. In line with this research, a Dutch study [30] recently showed that (a) exposure therapy is effective in the treatment of adults with complex trauma and (b) adding a non-trauma-focused component (affective and interpersonal regulation training) to the exposure therapy did not result in better outcomes. Interestingly, intensifying the exposure therapy resulted in faster symptom reduction. The faster reduction of symptoms is especially important for youth because posttraumatic stress hinders development [4] and adolescence is a critical period for social development, including peer influence [31]. There are also promising results in intensive trauma-focused treatment for adults that combined EMDR and imaginal exposure [32] and for adolescents who received intensive exposure therapy [33]. The characteristic of these intensive treatment programs is that the trauma treatment is given by different therapists. Therapist rotation is thought to decrease fear and avoidance behaviour of the therapist [34] and thereby increase treatment fidelity.

Besides offering trauma-focused therapy and intensifying the frequency in which these therapies are offered, trauma treatment might be enhanced by including trauma-focused bodily oriented therapy [35]. After trauma, children can experience flashbacks and intense emotions like fear, bodily sensations, and physical complaints [36]. According to Lang’s informational theory [37, 38] fear is an associated network of information based on previous experiences, developed to avoid or flight from danger in order to increase survival. This network is activated when confronted with a stimulus that matches information stored in this network. Based on these previous experiences, this stimulus is associated with a specific meaning and physiological and behavioural response [39]. For example, for someone who experienced a life-threatening fire, the sound of a siren could be a stimulus associated with danger and response elements like racing heart, muscle tensing, and hiding. These responses once were adaptive and promoted survival during the traumatic events but are now maladaptive [36]. Bodily oriented therapy, developed from clinical practice, is focused on the affective and behavioural components of these habitual responses. Combining trauma therapy with physical activities has been found associated with lower PTSD symptoms compared to trauma therapy without physical activities [40]. One randomized trial found that trauma-informed yoga reduced PTS symptoms [41]. These findings justify the inclusion of bodily oriented intervention components alongside other trauma-focused components.

Trauma-focused therapeutic components like EMDR and exposure may reduce PTS but may not automatically lead to improvements in parent functioning and the parent-child relationship. To achieve this, parental and systemic components are added to treatment programs like TF-CBT. Especially in situations of family violence that affect the whole family system, it is important to examine the value of adding parental and systemic components to EMDR and exposure. Meta-analytic data shows that interventions to reduce child maltreatment yielded larger effect sizes if focused on parental skills and social/emotional support than interventions without such focus [42]. Evidence that adding a parental component to individual trauma treatment increases treatment success, measured in children’s PTS symptoms, is also promising, yet inconclusive [28]. Few studies have systematically reviewed and/or meta-analytically examined the effectiveness trials that included interventions focusing on parenting factors in situations of family violence.

#### The added value of parent training and parent-child sessions

A systematic literature search ([name], [name], [name], [name] & [name]: An umbrella review on the added value of parent training and parent-child sessions in the treatment of family violence: how to promote improvement of parenting behaviour, the parent-child relationship and structural family safety, in preparation) revealed a limited but growing body of research on how parenting training and parent-child sessions may lead to changes in parenting behaviour, in the parent-child relationship, and especially in family safety. Four systematic reviews were identified on parenting-focused interventions for violence in families [43–46]. One meta-analysis [45] concluded that parent-child or parent intervention positively affects positive parenting behaviour and children’s functioning. There was no difference in effect between parent versus combined parent and child intervention but statistical power was too low. Another review [46] concluded that children with outside support fared better on behaviour problems, that improvement was stronger when offering more than five contacts to the family, and that changes in parenting behaviour and psychiatric symptoms were largely responsible for treatment effects on children’s conduct problems. It was not possible to draw unambiguous conclusions about how parent- and family-focused interventions affect parent functioning, child functioning, and the parent-child relationship due to the limitations of the reviewed studies. These limitations included the relatively large variation across studies in the manner that interventions were offered, in the types of intervention offered, and in the target of the intervention and outcome measures. Also, understanding the role of parenting and parent-child relationships within therapeutic interventions is hampered by methodological challenges, such as informant bias in the case of self-report instruments of parenting and relationships. Furthermore, there is a need for larger sample sizes, controlled study designs, protocolled treatments, and assessment of treatment fidelity [43]. Because of the great variations in type of interventions in the different studies, it is not possible to draw conclusions about the parental factors most important to cause changes in parent and child functioning and the parent-child relationship. There is some evidence that trauma-informed parenting interventions improving positive parenting skills are most important [45] and focusing on the support system and parental health is promising [46]. Most multicomponent treatments are focused on these factors [46]. To understand the added value of attention to parental factors in the treatment of family violence, studies are needed of (a) protocolled treatments; (b) treatments focused on specific parent components, like trauma-informed parenting, support, and parental health; (c) different types of instruments (observation, questionnaires, interview) and for multiple informants; (d) outcome measures for parenting behaviour, parent-child relationship, and family safety; (e) controlled study designs; (f) large study samples; and (g) assessment of treatment fidelity.

#### Family-based intensive trauma treatment

Because of the severe impact of family violence on children and their families and the complexity of family violence through the reciprocal influence of children’s PTS and parent and family functioning, we developed an intervention protocol that addresses these factors on an individual and family level in a short period of time: the family-based intensive trauma treatment (FITT). The goal of FITT is to establish long-term effects on the reduction of children’s trauma symptoms and recovery of security in the family. By first concurrently reducing children’s trauma symptoms and improving parenting functioning, the stage is set to increase the emotional and physical security in children through the improvement of the parent-child relationship.

FITT therefore consists of (a) intensive trauma treatment (exposure, EMDR, bodily oriented therapy) for the child; (b) individual parent therapy, based on the horizon method [47] (the Horizon-method is originally a group-based version of TF-CBT) [48], focusing on lowering parental stress and increasing trauma-sensitive and supportive parenting; and (c) family therapy focusing on sharing thoughts and feelings about the traumatic events, recognizing and breaking destructive patterns, and finding solutions for recurring problems.

#### Effectiveness study of FITT

This study examines to which extent FITT is an effective treatment for concurrent reduction of children’s trauma symptoms, improvement of parenting functioning, and enhanced emotional and physical security in children, through the improvement of parent-child relationships—in order to establish long-term effects on the reduction of trauma symptoms and recovery of security in the family. In this multi-centre study with a randomized controlled design, we compare FITT with an intensive trauma treatment without a parent and systemic component (ITT) and with treatment as usual (TAU) and low-frequency trauma treatment with parent therapy and family sessions). Comparing these interventions with and without specific components contributes to understanding if these interventions are effective and how these interventions work [49]. These insights may be used to increase treatment effectiveness [50] for adolescence with complex traumatic experiences. To further detect the mechanism of change, we included measurements during treatment [50].

### Objectives {7}

The primary objective is to examine the effectiveness of parental and systemic components that complement an intensive trauma treatment for children who have been exposed to family violence in the family. This objective translates into the following research question:
Does intensive trauma therapy for children with a family-based component (FITT) lead to a stronger reduction of trauma symptoms of children and a stronger increase of structural emotional safety than intensive trauma therapy without a family-based component (ITT)?

In addition, secondary objectives regard the elucidation of the intervention mechanism and effects on secondary outcomes. These objectives lead to the following research questions:
Does intensive trauma therapy for children with a family-based component (FITT) lead to faster reduction of trauma symptoms and increase of structural emotional safety than low-frequency trauma treatment with parent therapy and family sessions (TAU)?
After 4 weeks of treatment, does intensive trauma therapy for children with a family-based component (FITT) lead to a stronger reduction of trauma symptoms and a stronger increase of structural emotional safety than low-frequency trauma treatment with parent therapy and family sessions (TAU)?After the end of treatment, does intensive trauma therapy for children with a family-based component (FITT) lead to an equal reduction of trauma symptoms and an equal increase of structural emotional safety as in low-frequency trauma treatment with parent therapy and family sessions (TAU)?At the end of treatment, to what extent do we find the differences between intensive trauma therapy for children with a family-based component (FITT) and intensive trauma therapy without this family-based component (ITT) in trauma-informed parenting?

### Trial design {8}

This multicentre study is a parallel-group, randomized controlled component trial to examine (1) the addition of a component with parenting therapy and family sessions to an intensive trauma-focused therapy component and (2) the addition of an intensive component to a low-frequent trauma-focused therapy with parenting therapy and family sessions. This study is a superiority trial comparing FITT and TAU after 4 weeks of treatment and FITT and ITT at end of treatment and follow-up. The comparison between FITT and TAU at follow-up concerns an equivalence trial. This randomized controlled design includes follow-up with 96 (completer’s rate 80%) children and their caregiver(s) divided over two intensive trauma treatment arms and one treatment as a usual arm. The allocation rate for all comparisons is 1:1. The effectiveness trial comprises a pre-treatment, during treatment, end of treatment, and follow-up design.

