### Interventions

#### Explanation for the choice of comparators {6b}

Intensive trauma therapy (ITT) is the comparator of family-based intensive trauma treatment (FITT) to examine the addition of a component with parenting therapy and family sessions to an intensive trauma-focused therapy component. It is important to understand if this addition is more effective in reducing trauma symptoms, improving parenting functioning, and increasing emotional and physical security in children, through the improvement of parent-child relationships—and thereby establishing long-term effects on the reduction of trauma symptoms and continuation of security in the family.

The second comparator for FITT is treatment as usual (TAU) to examine the addition of an intensive component to a low-frequent trauma-focused therapy with parenting therapy and family sessions. This comparator examines if FITT is as effective as TAU at the end of treatment and if FITT results in faster symptom reduction. In the view of adolescence as a critical period for development and peer influence [51], this faster symptom reduction is of great importance.

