#### Sample size {14}

Power analysis was conducted to determine whether an informative trial could be conducted given limitations imposed upon the maximum sample due to the duration of the study and size of the population of children indicated for trauma treatment, using G*power 3 [95]. Sample size calculation was made based on the assumptions of the primary objective and the first secondary objective. A priori, we decided that adding systemic intervention elements to individual trauma therapy would be justified if it would mean that on average at least one out of five children would have clinically significant benefit when given the full FITT compared to treatment without systemic elements (number needed to treat = 5; equivalent to *f* = 0.18).

For primary objective 1 (Does intensive trauma therapy with a family-based component (FITT) lead to a stronger reduction of trauma symptoms and stronger increase of structural emotional safety than intensive trauma therapy without this family-based component (ITT)?), the sample size was calculated based on between 2 groups by within effect with at least two measurements (pre, end/follow-up), setting *f* = 0.18 with a power of 80% and a significance level of 5% (two-sided). Default settings were used for the correlation among repeated measures (= 0.5) and non-sphericity correction (*ε* = 1). According to the power analysis, a total sample size of 64 children is required.

Secondary objective 1 (Does intensive trauma therapy with a family-based component (FITT) lead to faster reduction of trauma symptoms and increase of structural emotional safety than low-frequency trauma treatment with parent therapy and family sessions?) is based on two measurements (pre and intermediate/follow-up). In accordance with the first sample size calculation, we tested with setting *f* = 0.18 with a power of 80%, a significance level of 5% (two-sided) was used. Again, default settings were used for correlation among repeated measures (= 0.5) and non-sphericity correction (*ε* = 1). Based on this calculation, a total sample size of 64 children is required.

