Descriptive and exploratory analyses will be carried out by standard methods. All continuous scores will be examined for normality. If variable distributions deviate too much from normality, corrective steps will be taken either by transforming variables or by using non-parametric tests. We will control for child functioning, parental psychopathology, duration, severity, and intensity of interparental violence, and new IPV incidents. The variables are treated as covariables in the analyses mentioned below.

To examine our primary hypothesis, linear mixed models will be used in case of continuous data. GEE will be used for the categorical data. We will use the end of treatment (T12/T14) and intermediate/follow-up time-point (T13) to compare FITT with ITT (objective 1).

To examine our secondary hypotheses, linear mixed models will be used. We will use the end of treatment time-point (T12/T14) to compare FITT with TAU. Control measures are child functioning; parental psychopathology; duration, severity, and intensity of interparental violence; and new IPV incidents. The variables are treated as covariables in the up-mentioned analyses. We will use the Benjamini-Hochberg method to correct for multiple comparisons.

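### The later FITT–TAU comparison is called an equivalence trial, but it has no margin, a superiority sample size, a difference-testing analysis and no single time point

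*Protocol article*

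**What the plan says.** **Design.** Trial design {8} separates two kinds of FITT–TAU comparison. The early one, at 4 weeks, is a superiority comparison. The later one is not: "The comparison between FITT and TAU at follow-up concerns an equivalence trial".

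**Question.** Objectives {7} asks whether, once treatment has ended, FITT will "lead to an equal reduction of trauma symptoms and an equal increase of structural emotional safety as in low-frequency trauma treatment". The rationale for the comparators {6b} puts it this way: "This comparator examines if FITT is as effective as TAU at the end of treatment and if FITT results in faster symptom reduction".

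**Size.** Sample size {14} covers the primary objective and the first secondary objective (faster improvement than TAU). Both calculations use f = 0.18, 80% power and a two-sided 5% level. For FITT–TAU: "Based on this calculation, a total sample size of 64 children is required". The effect size is justified by the number of children who "would have clinically significant benefit when given the full FITT compared to treatment without systemic elements", which is the FITT–ITT contrast.

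**Analysis.** Statistical methods {20a} uses linear mixed models to see whether change differs by treatment, and gives the secondary hypotheses the same models. On timing: "We will use the end of treatment time-point (T12/T14) to compare FITT with TAU". Follow-up (T13) is named there for FITT versus ITT only.

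**The concern.** An equivalence comparison needs three things that a superiority comparison does not: a margin, a rule that places the whole confidence interval inside it, and a size chosen so that this can happen. The article gives none of them for FITT–TAU. What it does give (f = 0.18, two-sided 5%, a model for differences) belongs to the opposite question.

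What is at stake is the second half of the argument for FITT over TAU, namely faster improvement that ends up as good. As planned, the trial can address the first half. For the second it offers only a test whose non-significance is uninformative at this size.

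The comparison also lacks a settled time point. The design section says follow-up. The comparator rationale and the analysis section say end of treatment. Read literally, the declared equivalence comparison has no assigned analysis at its declared time.

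**Working it through.** **1. The plan's own figure.** Inputs from Sample size {14}: f = 0.18, two groups, m = 2 measurements, ρ = 0.5, ε = 1, α = 0.05 two-sided. For the G*Power within–between interaction:

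λ = f²·N·m/(1 − ρ) = 0.0324 × 64 × 2/0.5 = 8.29, with 1 and 62 degrees of freedom.

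Power is 0.809 at N = 64 and 0.796 at N = 62, so 64 is the smallest even N that reaches 80%. Three arms of 32 make 96 completers, and 96/0.8 = 120 randomised. All the stated figures reproduce, and all are superiority figures.

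**2. What f = 0.18 means in SD units.** There are two readings.
- d = 2f = 0.36. Then NNT = 1/(2Φ(0.36/√2) − 1) = 4.98, which agrees with the stated NNT of 5.
- Under the formula that yields 64, the difference in change is √(4λ/N) = √(4 × 8.29/64) = 0.72 SD of change.

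Neither is offered as an equivalence margin. They are used below as assumed margins, with 0.5 SD between them.

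**3. Precision with 32 completers per arm.** SE = SD·√(2/32). The SD is assumed to be 1 for a change score (at ρ = 0.5 the change score has the same SD as the raw score), or √(1 − 0.5²) = √0.75 = 0.866 if adjusted for baseline.
- SE = 0.250 or 0.217.
- 90% CI half-width = 1.67 × SE = 0.42 or 0.36 SD.

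**4. What a difference test would show, and what an equivalence test could show.** Non-significance is from the noncentral t distribution, two-sided 5%. Equivalence is by two one-sided tests at 5% each, exact t, with a true difference of zero. Each cell gives change score / baseline-adjusted.

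| Size (SD) | P(non-significant) if FITT is truly worse by this much | Power to show equivalence within this margin |
|---|---|---|
| 0.36 | 71% / 63% | 0.3% / 4.7% |
| 0.50 | 50% / 38% | 26% / 48% |
| 0.72 | 19% / 9% | 77% / 90% |

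For 80% power on the change score, the completers needed per arm are 133, 70 and 34 at these three margins, against 32 planned.

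**5. Time point.**

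| Section | Time for the later FITT–TAU comparison |
|---|---|
| Trial design {8} | Follow-up |
| Comparators {6b} | End of treatment |
| Statistical methods {20a} | T12/T14 (end of treatment) only |
| Objectives {7} | After treatment has ended; could mean either |

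The firm conflict is between {8} on one side and {6b} and {20a} on the other.

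**The case against.** The strongest reply is that the article never says a non-significant result will be taken as equality. That is true. A reader might infer such a rule because no other is given for the equality question, but the documents do not state it, and it should not be attributed to the authors. A mixed model also produces an estimate and an interval from which equivalence could be judged, and a decision rule may sit in an analysis plan that is not shown. So the model is not wrong in itself. What survives is that the margin and the size that goes with it are design parameters, and the sample size section gives a superiority calculation instead.

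A second reply concerns 0.36 SD. A reader might treat it as the plan's own smallest important difference and conclude that FITT would usually pass as equal even if materially worse. The documents do not support that. The value is justified for FITT versus ITT only, and f = 0.18 can equally be read as 0.72 SD of change. Non-significance is the usual outcome at a true deficit of 0.36 SD. At 0.5 SD it occurs in half the trials or fewer, and at 0.72 SD in fewer than one in five. Under the 0.72 SD reading, equivalence power is near or above 80%.

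Third, the objectives need not contradict the design section on timing, since follow-up also comes after treatment. That stands.

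Finally, this is one secondary sub-question, and the protocol says openly which objectives the size was based on. That bears on weight, not on whether the label fits.

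**Conclusion.** The point holds for the later FITT–TAU comparison only. It is declared an equivalence trial without a margin, is sized for superiority, is assigned a test of difference, and is placed at different times in different sections. The contradiction is in the text and does not depend on any assumed number.

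Its size does depend on assumptions: 32 completers per arm, an SD of 1 or √0.75, ρ = 0.5 and margins that the protocol does not supply. Across those, equivalence is practically out of reach at 0.36 SD, unlikely to be shown at 0.5 SD (below 50% power), and roughly adequately powered only at about 0.72 SD. Other model covariates could improve these figures, but the article gives no value for their effect.

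This should be corrected, but it is not critical to the trial. The primary FITT–ITT comparison and the 4-week superiority comparison are not affected.

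**What to change.** **Preferred.** In Objectives {7}, Trial design {8}, the comparator rationale {6b} and Statistical methods {20a}, name one and the same time point for the later FITT–TAU comparison. Replace the equivalence label by estimation: report the FITT–TAU difference with its 95% confidence interval, and state that a non-significant difference will not be read as equality.

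**Alternative.** Keep equivalence, but state a justified margin in score units for a named outcome at that time point. Conclude equivalence only if the 90% confidence interval lies wholly inside the margin, and report the power that the planned size gives for it.

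**Cost.** Wording only for the first option, with no added participants; the equivalence claim is given up. The second option keeps the claim, but at 32 completers per arm it has little power unless a wide margin can be defended.
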